#### Type of statistical analysis used

To test the aforementioned hypotheses, first, a propensity score matching will be applied between the IG and the CompG. Sensitivity analyses and test–retest reliabilities will be used to test Hypothesis 1 and 2 respectively. To test Hypothesis 3, MANOVA and repeated measurement ANOVAs will be used. To assess Hypothesis 4, no statistical analyses but a qualitative approach will be used. For the last hypothesis (Hypothesis 5), repeated measurement ANOVAs and MANOVAs will be used.

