## Methods

### Study design and setting

This longitudinal randomized control trial study will take place in Bavaria in Germany and has three study arms. Specifically, patients will be randomly assigned to an intervention group (IG) or an active control group (ACG, see Fig. 3 for the flow chart). Furthermore, a comparison group (CompG) will be recruited. Whereas the CompG will not receive any treatment, the IG and the ACG will have contacts with a *personal pilot* who will help the patients to navigate the study participation as well as through treatment options and help them seek help for further needs. The personal pilot acts as a contact point for patients and service providers and guides patients through the care process. Furthermore, the personal pilots make sure participants will take part in the study questionnaires by continuously reminding the patients in case they did not fill out the questionnaires.

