Internal diagnostics	• Echography • Carotis-duplex sonography

The results of the assessment for each professional group will be handed to a clinician, who is then able to make a holistic assessment of whether PACS is present or not. These assessments are also summarized to form a holistic treatment plan, which synopsizes the findings and lists the indicated medical and therapeutic measures. These recommendations will be made visible for the personal pilot, and subsequently made available to the attending outpatient doctor.

The prescription of necessary treatments and aids, as well as the recommendation of digital interventions already take place within the framework of discharge management. If the need for a rehabilitation measure is determined, this will be communicated to the patient directly in a way to enable him/her applying for rehabilitation treatment and finding the most appropriate treatment within Germany (also with the help of the personal pilot).

Using such an approach allows us to test Hypothesis 2, that a comprehensive assessment can determine rehabilitation or remedial needs and the leading rehabilitation indication. To assess the applicability of this hypothesis, we will consider a comparison of test–retest reliabilities of the degree of experienced symptoms in the IG compared with the ACG and the CompG. Furthermore, the assessment allows us also to test Hypothesis 5 that an interdisciplinary treatment pathway empowers the patient. To assess the applicability of this hypothesis we will check whether IG, ACG and CompG differ in terms of the development of symptoms, increased activities of daily lives, RTW and increased social participation. To do so, we will consider MANOVA and repeated measurement ANOVA analyses.

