Using this method and determining differences in the IG (patients who receive individualized digital offers on basis of their physical resilience), ACG (patients who received individualized  offers based on the most debilitating symptoms) and CompG (patients who only received the chatbot on a voluntary basis) in the questions about how effective they found the digital interventions in the treatment of PACS allows us to test Hypothesis 3. Within this hypothesis, it is assumed that the more individualizable digital interventions are, the better they work. To assess this, we will check whether IG, ACG and CompG differ in terms of the development of symptoms, increased activities of daily lives, RTW and increase social participation with individualization as another factor. To do so, we will consider MANOVA and repeated measurement ANOVA analyses considering individualization accordingly.

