### Evaluation concept

A longitudinal randomized control trial design is used in this project with a three-group pretest–posttest procedure. Whereas the CompG will be recruited with different links via online invitations (e.g., via social media campaigns), the IG and the ACG are recruited with another separate link. After agreeing to take part in the study, participants will be randomized by throwing a dice. Patients for whom a 1 or 2 was rolled are placed in the IG and patients for whom a 3–6 was rolled are placed in the ACG. If a randomization cannot be realized (e.g., because they cannot take part in the stationary assessment due to organizational limitations), patients will be allocated to the ACG but will be marked for statistical analyses. Methodically, a propensity score matching will be used between the IG and the CompG to ensure the comparability of these groups (i.e., participants will statistically be matched by various person-related criteria such as age and sex). All groups are repeatedly interviewed with similar instruments in each group (see Table 1). Time points of measurement are the screening (T1), prior to the assessment in the IG and a comparable time point in the ACG (T2), after the assessment in the IG and at a comparable time point in the ACG (T3). Then approximately 6 weeks after T3 and after symptom-specific digital interventions, a further measurement will take place (T4). Another 6 weeks later a follow-up measurement will take place (T5). A last measurement time point (T6) will be conducted 6 months later with some selected participants. All time points of measurement are included in the study flow chart (Fig. 3).

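### The randomised IG v ACG test is not kept apart from the propensity matching or from the non-randomised CompG, and what CompG receives is described in two ways

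*Protocol article*

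**What the plan says.** All places are in the protocol article.

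- **Order and scope of the matching** (Type of statistical analysis used): "To test the aforementioned hypotheses, first, a propensity score matching will be applied between the IG and the CompG". No exception is made for IG v ACG. The same paragraph assigns MANOVA and repeated-measures ANOVA to Hypotheses 3 and 5.
- **Purpose of the matching** (Evaluation concept): "Methodically, a propensity score matching will be used between the IG and the CompG to ensure the comparability of these groups". ACG is not named. The criteria are given by example: "participants will statistically be matched by various person-related criteria such as age and sex".
- **Comparison for Hypothesis 5** (2. Comprehensive assessment program): "To assess the applicability of this hypothesis we will check whether IG, ACG and CompG differ in terms of the development of symptoms".
- **Comparison for Hypothesis 3** (3. Digital therapy offers): "To assess this, we will check whether IG, ACG and CompG differ in terms of the development of symptoms", with individualisation as a further factor.
- **Allocation** (Evaluation concept): CompG is recruited through its own online links. A dice throw of 1 or 2 gives IG and 3 to 6 gives ACG. Patients who cannot be randomised go to ACG and are marked for the analysis.
- **Sample size** (Sample size planning): 66 IG and 66 ACG, two-sided alpha 0.05, power 68%. No CompG number is given.
- **What CompG receives**: Study design and setting says "Whereas the CompG will not receive any treatment", and the Abstract agrees. Section 3. Digital therapy offers describes CompG as "patients who only received the chatbot on a voluntary basis". The Abstract lists the chatbot as part of the treatment given to IG and ACG.

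**The concern.** The trial contains one randomised contrast, IG v ACG, and two observational ones, IG v CompG and ACG v CompG. The plan sizes the first, but describes the tests of Hypotheses 3 and 5 as comparisons of all three groups and puts a matching step for one observational pair in front of them. Nothing marks IG v ACG as a test of its own, run on the patients as randomised.

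Two things are at stake. A significant result for Hypothesis 3 or 5 could be read as evidence for the assessment and individualised pathway when it reflects only who chose to join CompG. And the unbiased contrast could be altered by a step that it does not need.

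The conflicting descriptions of CompG are a separate matter. They affect what any CompG contrast estimates, and they matter for Hypothesis 3, where the amount of individualisation is the factor under study.

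**Working it through.** **1. What the three-group test can detect.** Let the mean change over time be μ in both IG and ACG, and μ + δ in CompG. The hypothesis of no group-by-time interaction is then false whenever δ ≠ 0, although IG and ACG do not differ. CompG is self-selected through separate links, so δ may contain confounding. A significant three-group result therefore does not by itself say that IG differs from ACG.

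**2. What the matching does for ACG v CompG.** Let x_R be the mean of a measured covariate in the randomised population and x_N its mean in the patients who could not be randomised. Let r be the share of ACG made up of the latter. If CompG is matched to a fully retained IG, CompG sits near x_R. ACG has mean (1 − r)·x_R + r·x_N. The remaining ACG–CompG imbalance is r·(x_N − x_R).

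- If r = 0, randomisation carries the balance over to ACG in expectation.
- If r > 0, part of the imbalance remains unless the marked patients are set aside. The article gives neither r nor how the marking will be used.
- Covariates left out of the matching are not covered in either case.

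**3. What is lost if unmatched IG patients are dropped.** The article does not say that they are, so the losses below are assumed. The variance of IG v ACG is proportional to 1/n_IG + 1/n_ACG. The 44:88 split is also an assumption: it is the expected result of the dice ratio at N = 132 (132 × 1/3 = 44).

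| Assumed IG loss | 66:66, n_IG | Variance factor | 44:88, n_IG | Variance factor |
|---|---|---|---|---|
| 10% | 59.4 | 1.06 | 39.6 | 1.07 |
| 20% | 52.8 | 1.125 | 35.2 | 1.17 |
| 30% | 46.2 | 1.21 | 30.8 | 1.29 |

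Example: (1/52.8 + 1/66) / (1/66 + 1/66) = 0.03409 / 0.03030 = 1.125.

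**4. The same losses as power.** The stated 68% has no unique reproduction, because the article gives neither the number of measurements nor their correlation. Two unstated settings come close:

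- 0.15 read as Cohen's f, two measurements, correlation 0: 67.7%.
- 0.15 read as d (f = 0.075), three measurements, correlation 0.7: 67.2%.

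I therefore use 68% only as a benchmark. With N_eff = 4·n_IG·n_ACG/(n_IG + n_ACG) and a normal approximation, power = Φ[(1.960 + 0.468)·√(N_eff/132) − 1.960].

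- 66:66 with losses of 10/20/30%: N_eff = 125.1/117.3/108.7, power about 66/63/60%.
- 44:88 with no loss: N_eff = 117.3, power about 63%. With losses of 10/20/30%: N_eff = 109.2/100.6/91.3, power about 60/56/52%.

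These figures cover precision only. Selection bias from dropping the IG patients least like CompG would be added, with unknown sign.

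**5. CompG exposure.** No treatment (Abstract; Study design and setting) and voluntary chatbot use (3. Digital therapy offers) cannot both describe the group, because the Abstract treats the chatbot as an intervention.

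**The case against.** The best defence is that the matching was meant only for the CompG contrasts. Evaluation concept gives its purpose as making IG and CompG comparable, and Sample size planning treats IG v ACG as a two-group comparison without CompG. The wording that puts matching first for the hypotheses cannot be meant literally. Hypothesis 4 is qualitative, and Hypothesis 1 sets the screening against decisions made after an assessment that only IG receives, so neither can use a match to CompG. Matching ratio, caliper, handling of unmatched patients and follow-up contrasts are usual content of a fuller plan.

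Much of this stands. A reader might infer that randomised IG patients will be discarded. The article does not say so, and if every IG patient finds a match, none is lost. A reader might also infer that confounding between ACG and CompG is left wholly untouched. That goes too far, because randomisation can carry balance from IG to ACG. Nor does the text fix age and sex as the only matching variables; they are examples. It also does not say that an omnibus p-value alone will be the efficacy claim.

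What does not fall away is the wording that the article fixes. Matching comes first, it covers one pair only, and the tests of Hypotheses 3 and 5 are described across three groups with no separate randomised test. The two descriptions of CompG are a plain contradiction and do not depend on this argument.

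**Conclusion.** The point holds as a failure to separate the randomised comparison from the observational ones.

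- **Firm, from the text alone:** a three-group effect can come from CompG self-selection; ACG v CompG is not directly matched, and any balance inherited through randomisation is weakened by the non-randomised patients in ACG; the descriptions of CompG conflict.
- **Conditional:** loss of the randomised basis of IG v ACG occurs only if unmatched IG patients are dropped. For assumed losses of 10/20/30%, the variance rises by about 6/13/21% at the stated 66:66, or 7/17/29% if the dice ratio gives 44:88. Power then falls from the benchmark 68% to about 66/63/60%, or from about 63% to 60/56/52%.

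The size of any CompG confounding cannot be calculated from the article.

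**What to change.** 1. State that the efficacy test for Hypotheses 3 and 5 is IG v ACG alone, in all randomised patients, without matching and without the marked non-randomised ACG patients. State that the marking is for patients for whom no dice was thrown, so that no randomised patient leaves the analysis.
2. Compare CompG with IG and with ACG in a separate analysis labelled observational. Match or weight CompG to the randomised population without discarding randomised patients. Use items that the screening (T1) is said to collect: symptoms, infection timeline, previous treatment, age and sex. Add work status only if it is collected at baseline; the article's list of screening items does not include it.
3. Do not use the three-group omnibus test as evidence of efficacy.
4. Reconcile the Abstract and Study design and setting with 3. Digital therapy offers, so that CompG's exposure is described once.

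The cost is a change of wording, a little extra analysis and a more modest claim for the CompG contrasts. No new data are needed unless work status is wanted and is not yet collected at baseline.

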## Discussion

The study aims to implement a comprehensive care process for people with post-acute COVID-19 syndrome (PACS) based on theory and evidence. This includes four components: (a) a low-threshold online screening to identify as many individuals as possible with a possible PACS, (b) a physiological and psychological assessment as well as (c) digital interventions as supporting formats within a support system over several weeks and (d) personal pilots supporting the patients to make effective use of the health care system by means of empowerment and guidance. The entire process is aimed at supporting the patient through a personal pilot who acts as the first point of contact for the patient. The personal pilot also coordinates and implements the treatment plan, and after the interventions, supports the patient to find additional and potentially necessary treatment options (i.e., rehabilitation treatment, psychotherapy treatments or other treatment options). In addition, the pilot acts as an executive to also inform all the medical service providers that are included in the screening, assessment, and provision of digital interventions by means of dissemination.

### Dissemination of the study results

After completion of the study project, a large network of outpatient and inpatient providers will have been established who offer the treatment to patients with suspected PACS. If the effects of the personal pilot and the digital training interventions transpire successfully, this provides evidence that such a support system may pay off, especially in times of people in need where no services are available at their convenience.

The aim of the current study is to enable the decision-making processes and the evidence-based treatment of PACS patients in the general population with their diverse and individual complaints in the long term, to discharge them from treatment into their everyday lives, and to reintegrate into society. To do so, a *manual* that includes a description of the contact session between the personal pilot and the patient will be made freely available after the completion of the project to ensure continuous and standardized care according to a well-established and valid process for individuals diagnosed with PACS. To ensure the future care for individuals with PACS, any doctor can introduce patients into the treatment pathway; we believe that what is needed is contact with the personal pilot. Service providers who meet the professional and structural requirements for interdisciplinary and holistic assessment and treatment planning in the sense of the bio-psycho-social model can guide the treatment with a high level of quality.

The comprehensive care process should be able to be transferred to regular care and other illnesses and, after the study is completed, will be presented in a corresponding concept (*white paper*) for diagnostics and care specifically for the target group along with the manual for the personal pilots. Our project, which is intended to close a relevant gap in care, has the potential to not only be transferable regionally, but nationwide and internationally.

The results regarding the hypotheses will be disseminated in scientific publications, which will be communicated to experts and the public by means of press work and social media.

This study will also provide valuable information on the effectiveness, user acceptability, and feasibility of the different components. It addresses the need to investigate new approaches to improve health care provision and support of vulnerable patients, which can relieve health systems from the growing demands caused by challenges with communication around the world and in all areas of medicine and public health.

## Data Availability

The data for this study will not be publicly available due to data protection guidelines. The data will be available on reasonable request from the corresponding author and stored on secured servers of the Jacobs University Bremen gGmbH. Newly developed interventions will be made available on open access servers by the end of the project.

## Abbreviations

ACG: Active control group
ADL: Activities of daily living
ASAP: Assistierter Sofortiger Augmentierter Post-/Long-COVID Plan [Assisted Immediate Augmented Post-/Long-COVID Plan]
CCAM: Compensatory Carry-Over Action Model
CompG: Comparison group
GP: General practitioner
ICF: International Classification of Functioning
IG: Intervention group
NICE: UK National Institute for Health and Care excellence
PACS: Post-acute COVID-19 syndrome
RTW: Return to work
SEP: Somatosensory evoked potentials
SNAP: Smoking, nutrition, alcohol, physical activity
